## Methods

### Aims and objectives

This randomized controlled study aims to improve treatment outcomes in participants with TUD by enhancing cognitive control and sleep quality, thereby counteracting the hypothesised imbalance in regulatory control towards the habit system (see Fig. 1). This study further aims to identify the most effective pathway by which increased cognitive control promotes smoking cessation and thus reduces the risk of relapse. Two interventions will therefore be tested alongside the standard smoking cessation program, resulting in four intervention groups. One intervention will focus on improving sleep quality through app-based HIIT either in the morning or the early evening. The other intervention will involve CRT via an app-based chess training program either in the morning or early evening.

**Fig. 1 Fig1:**
[figure not shown]
Schematic display of the study rational. The study aims to improve treatment outcomes in participants with TUD by enhancing cognitive control and sleep quality, thereby counteracting the hypothesised imbalance in regulatory control towards the habit system

We hypothesise that a combination of CRT and HIIT in the evening will enhance treatment outcomes to a greater extent than sleep enhancement via HIIT alone or a combination of CRT and HIIT in the morning. This will be reflected in more abstinence days or fewer cigarettes smoked following relapse. Furthermore, we hypothesise that improved cognitive control is mirrored in improved behavioral results in neuropsychological tasks and changes in neural activity, e.g., during tasks assessing response inhibition or working memory. We predict that these changes are associated with both craving and treatment outcomes.

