**Methods:**

The study will enrol 140 treatment-seeking smokers aged 18–65 years who meet the DSM-5 criteria for TUD. The participants will be randomly assigned to four groups: CRT + HIIT in the morning, CRT + HIIT in the evening, HIIT alone in the morning, and HIIT alone in the evening. Assessments will be conducted at baseline (T1), postintervention (T2), and at a three-month follow-up (T3) at the Central Institute of Mental Health in Mannheim, Germany. The primary outcomes include abstinence days or amount of alcohol consumed in cases of relapse, as well as craving reduction. Secondary outcomes include improvements in cognitive functions (working memory, response inhibition, and cognitive control), measured through neuropsychological tasks, functional magnetic resonance imaging (fMRI), polysomnography, and self-report questionnaires. The repeated-measures design allows for within-subject comparisons to evaluate intervention effectiveness.

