### Hypotheses

Primary hypotheses and treatment outcomes:

A combination of CRT + sleep enhancement (i.e., CRT + HIIT early evening) as a six-week add-on therapy enhances treatment outcomes (i.e., relapse and craving) in smokers in comparison to CRT (i.e., CRT + HIIT morning) or sleep enhancement (i.e., no CRT + HIIT early evening) alone.The changes in neural measures of response inhibition, working memory and network connectivity in the salience network following the six-week treatment from baseline will be associated with self-reported craving and perceived stress, as well as treatment outcomes.

2.Secondary hypotheses and mechanisms:

Improvement in cognitive function in smokers.

c.CRT, as a six-week add-on training, improves cognitive function in smokers (i.e., CRT + HIIT in the morning versus HIIT in the morning).

d.Sleep enhancement (induced by HIIT in the evening) as a six-week add-on training improves cognitive function in smokers (i.e., HIIT in the evening versus HIIT in the morning).e.The combined effect of sleep enhancement and CRT (i.e., the interaction effect of CRT × sleep enhancement) increases cognitive function even further.

Improvement in neuronal abnormalities.

f.CRT alleviates neural dysfunction during cognitive performance in smokers (i.e., CRT + HIIT in the morning versus HIIT in the morning).g.Sleep enhancement as a six-week add-on therapy ameliorates neural dysfunction during cognitive performance in smokers (i.e., HIIT in the evening versus HIIT in the morning), as reflected by neural measures of response inhibition, working memory and connectivity strength within the salience network.h.The combined effect of both training methods is even greater (i.e., the effect of CRT + HIIT in the evening versus HIIT in the morning).i.CRT as well as sleep enhancement (i.e., HIIT in the early evening) as a six-week add-on therapy reduces connectivity strength in the salience network.

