A total of 128 participants will be randomized into four groups (4 × 32 smokers), receiving add-on interventions alongside a smoking cessation program (SCP) [50]. The randomization protocol will control for sex. Stratified (men/women) block randomization with permuted blocks of size 8 will be used. Groups 1 and 2 will receive CRT + HIIT either in the evening or morning, respectively. Group 3 and Group 4 will receive only HIIT in the evening or morning, respectively. Each subject will undergo three days of investigation. Assessments will occur before SCP (baseline, T1), after a six-week SCP (T2), and at a follow-up appointment three months later (T3). An in-house smartphone application will be used to remind participants about the exercises and to collect accompanying information, i.e., physical exertion (every training day), cigarette craving (3 times per week), and evaluation of the three interventions (three days per week). Instances of relapse and any sleep or physical problems can also be reported. These data will be stored on local servers at the institute, and no personal information will be collected. Between T2 and T3, biweekly telephone screenings will be conducted to assess abstinence or relapse, as well as the amount of cigarette consumption. See study schedule, Fig. 2.

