### Sample size

The sample size was calculated via the software package G*Power (version 3.1.9.4 [51]) on the basis of the number of days of abstinence at posttreatment (day 42). With a sample size of 128 participants (32 participants per group), we achieve a power of 80%, assuming a minimum effect size of f = 0.25 in an ANOVA at a 5% alpha level. This ensures an optimal balance of sample size, information gain, and resource allocation [52]. To account for potential dropouts, three participants per group will be added, resulting in a total population of 140 participants.

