### Statistical analyses

Primary outcome measures include [1] treatment outcome (i.e., abstinence rates) after a six-week intervention phase compared with baseline; [2] improvement in cognition and thus changes in neural measures of response inhibition, working memory and salience network connectivity in relation to craving, perceived stress and treatment success. After preprocessing, including movement correction and normalization to the Montreal Neurological Institute template, the echo planar images will undergo spatial smoothing with a Gaussian kernel of 8 mm full width at half maximum. The analysis will be conducted at both the single-subject and group levels via the general linear model approach. For resting-state analysis, the seed region is the right anterior insula for the salience network, which is one of the two core regions anchoring the salience network [95]. At the second level of analysis, paired t tests will be used to observe the effects of groups and time (preintervention vs. postintervention within one group). Additionally, full factorial models will be employed. Regression models incorporating various clinical variables, such as the severity of TUD, will also be calculated. Correction for statistical testing will be performed via familywise error correction at the level of *P* < 0.05. EEG data during sleep will be analysed via an in-house script in python, resulting in hypnograms and information, such as the timing and length of sleep stages, as well as spectrograms, including information on activation and frequency at specific electrodes.

SPSS (Statistics for Windows, IBM Corp., Armonk, NY) and R (R: A language and environment for statistical computing. R Foundation for Statistical Computing, Vienna, Austria) will be utilized to analyse physiological (e.g., heat rate during HIIT), psychometric (e.g., questionnaire data) and neuropsychological data. Multivariate analyses of variances with repeated measures will be conducted to analyse the dependent variables. Additionally, linear regression models will be employed to examine the influence of confounding variables on changes in the dependent variables. Finally, Cox regression analyses, such as examining brain activation in the dorsolateral prefrontal and/or inferior frontal regions during inhibition, will be performed to evaluate associations with possible relapse.

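### Cigarette consumption is defined as an outcome only after relapse, so comparing arms on it would not be a randomised comparison and would omit the benefit of prevented relapse

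*Protocol article*

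**What the plan says.** Two places tie consumption to relapse.

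- **Aims and objectives** (text below Fig. 1), on the expected advantage of the combined evening arm: "This will be reflected in more abstinence days or fewer cigarettes smoked following relapse".
- **Abstract, Methods**: "The primary outcomes include abstinence days or amount of alcohol consumed in cases of relapse, as well as craving reduction". The word alcohol is a separate slip in a tobacco trial; the Aims text shows that cigarettes are meant.

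Three places describe the main outcome without consumption among relapsers.

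- **Hypotheses**: the combination "enhances treatment outcomes (i.e., relapse and craving) in smokers in comparison to CRT" or sleep enhancement alone.
- **Statistical analyses**: "treatment outcome (i.e., abstinence rates) after a six-week intervention phase compared with baseline".
- **Sample size**: the calculation was made "on the basis of the number of days of abstinence at posttreatment (day 42").

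Data collection is not restricted to relapsers. Between T2 and T3, "biweekly telephone screenings will be conducted to assess abstinence or relapse, as well as the amount of cigarette consumption" (Study population and design). Table 1 lists the number of cigarettes at T1, T2, I1-6, FU1-5 and T3.

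**The concern.** The primary hypothesis compares randomised arms, and lowering relapse is a stated aim. A measure that exists only for people who have relapsed leaves out those who stayed abstinent, who are the successes of treatment. The relapsers in one arm need not resemble the relapsers in another, because the add-on may have changed who relapses. Two things follow:

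- The contrast answers how much people smoke once they have failed, not whether the add-on reduces smoking. Relapse that was prevented earns nothing.
- The contrast is open to selection after randomisation, which could add to a real effect or hide it.

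The *or* in both statements adds to the risk. If abstinence days showed no difference, a contrast among relapsers could still be presented as meeting the hypothesis.

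**Working it through.** **1. The plan's own figure.** The Sample size section says: "With a sample size of 128 participants (32 participants per group), we achieve a power of 80" per cent, "assuming a minimum effect size of f = 0.25 in an ANOVA at a 5% alpha level". With the noncentral F distribution, λ = N·f² = 128 × 0.0625 = 8. With 1 numerator and 124 denominator degrees of freedom (a main effect or the interaction of the 2×2 layout), power is 0.801 and the minimum N is 128, so the figure reproduces. It concerns days of abstinence, which is defined for everyone randomised, so nothing below changes it.

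**2. Inputs for an illustration.** The document gives no mean or SD for consumption and no relapse rate by arm. The following are assumptions:

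- consumption of about 12 cigarettes/day, SD 5;
- relapse of 75% in the comparator (the Background gives about 75% at six months, a different time point) and 60% or 50% in the better arm;
- no effect of treatment on the amount smoked once relapsed;
- correlation ρ between relapse tendency and amount smoked of 0 to 0.7.

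**3. Formula.** Let relapse occur when a standard normal tendency exceeds c, with relapse probability r. Let consumption be 12 + 5S, where S is standard normal and correlates ρ with the tendency. Then mean consumption among relapsers is 12 + 5ρ·φ(c)/r. Over everyone randomised, with abstainers at zero, it is r times that.

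- r = 0.75: φ(c)/r = 0.3178/0.75 = 0.424
- r = 0.50: φ(c)/r = 0.3989/0.50 = 0.798

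The shift among relapsers is 5ρ × (0.798 − 0.424) = 1.87ρ, which is 0 at ρ = 0 and 1.31 at ρ = 0.7. Over everyone at ρ = 0, the change is 0.50 × 12 − 0.75 × 12 = −3.0.

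**4. Results.** A simulation of 2,000,000 draws, with consumption floored at 1 cigarette/day, agrees. Values are better arm minus comparator, in cigarettes/day.

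| ρ | Relapsers only, 75%→60% | Relapsers only, 75%→50% | All randomised, 75%→60% | All randomised, 75%→50% |
|---|---|---|---|---|
| 0 | 0.00 | 0.00 | −1.80 | −3.01 |
| 0.3 | +0.33 | +0.56 | −1.70 | −2.88 |
| 0.5 | +0.55 | +0.93 | −1.63 | −2.80 |
| 0.7 | +0.77 | +1.31 | −1.55 | −2.71 |

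**5. Adding a true benefit of 1 cigarette/day once relapsed** (relapse 75% to 50%). The contrast among relapsers is −1.00 at ρ = 0, −0.07 at ρ = 0.5 and +0.31 at ρ = 0.7. The sign changes only in that last, strongest case; at 75% to 60% and ρ = 0.7 it is still −0.23.

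**6. Numbers available.** Of 32 per group, 24 relapse at 75%, about 19 at 60% and 16 at 50%. This reduction applies to the relapser contrast only.

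**The case against.** The strongest reply is that the article specifies no analysis restricted to relapsers. The Aims sentence is a prediction, and the Statistical analyses section names no such subset. Someone who has quit can smoke only with or after relapse, so the phrase could be meant as a count over everyone, with abstainers at zero. Consumption given relapse is also marginal: only the abstract calls it primary, and then as an alternative to abstinence days, which does capture prevented relapse. The other three sections do not list it.

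Much of this stands. The article does not commit the trial to a relapser-only model, and Table 1 and the telephone screenings point towards data on everyone. But the abstract's wording is a stated outcome definition, not a detail left to another document, and the Aims text repeats the condition. The zero-counting reading is possible but is not what the words say.

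A reader might also infer that the effective arm will be left with its heaviest smokers and its effect understated. The document does not support that. It gives no link between relapse tendency and amount smoked. Without a link there is no selection shift. If the add-on mainly rescues heavier smokers, the shift reverses. If cigarettes are totalled from relapse onwards, later relapse shortens the count and favours the better arm.

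**Conclusion.** The point holds in limited form. As worded in the abstract and the Aims, consumption is conditioned on an event after randomisation that treatment is meant to alter. A comparison of arms on that measure would not be protected by randomisation and would omit prevented relapse. Under the assumed values, with relapse cut from 75% to 50%, it shows the better arm as 0 to 1.3 cigarettes/day worse, while consumption over everyone falls by about 2.7 to 3.0 per day. The omission appears in every scenario. The adverse shift requires that people more prone to relapse also smoke more.

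Two further inferences should be avoided. The stated power is not undermined, because it rests on days of abstinence. Nor should the shift be expressed as a share of f = 0.25: that effect size belongs to abstinence days, the document assumes no effect on consumption, and the primary contrasts are between single arms of 32. The wording should be changed before analysis; the flaw touches one component of the primary outcome.

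**What to change.** In the abstract and in the Aims text, define consumption as cigarettes smoked over fixed windows (start of treatment to day 42, and T2 to T3) in all randomised participants, with abstinent days counted as zero. Keep consumption among relapsers as a descriptive summary. Align both statements with the Hypotheses, Sample size and Statistical analyses sections, so that it is clear whether abstinence days or consumption decides the primary comparison.

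No new data are needed, because Table 1 already schedules the number of cigarettes at every relevant point without restriction to relapsers. The cost is rewording and a little analysis work. The one drawback is a distribution with many zeros (25% to 50% of participants in the 75% to 50% illustration), which calls for a rank-based or count-type analysis.

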### Hypotheses

Primary hypotheses and treatment outcomes:

A combination of CRT + sleep enhancement (i.e., CRT + HIIT early evening) as a six-week add-on therapy enhances treatment outcomes (i.e., relapse and craving) in smokers in comparison to CRT (i.e., CRT + HIIT morning) or sleep enhancement (i.e., no CRT + HIIT early evening) alone.The changes in neural measures of response inhibition, working memory and network connectivity in the salience network following the six-week treatment from baseline will be associated with self-reported craving and perceived stress, as well as treatment outcomes.

2.Secondary hypotheses and mechanisms:

Improvement in cognitive function in smokers.

c.CRT, as a six-week add-on training, improves cognitive function in smokers (i.e., CRT + HIIT in the morning versus HIIT in the morning).

d.Sleep enhancement (induced by HIIT in the evening) as a six-week add-on training improves cognitive function in smokers (i.e., HIIT in the evening versus HIIT in the morning).e.The combined effect of sleep enhancement and CRT (i.e., the interaction effect of CRT × sleep enhancement) increases cognitive function even further.

Improvement in neuronal abnormalities.

f.CRT alleviates neural dysfunction during cognitive performance in smokers (i.e., CRT + HIIT in the morning versus HIIT in the morning).g.Sleep enhancement as a six-week add-on therapy ameliorates neural dysfunction during cognitive performance in smokers (i.e., HIIT in the evening versus HIIT in the morning), as reflected by neural measures of response inhibition, working memory and connectivity strength within the salience network.h.The combined effect of both training methods is even greater (i.e., the effect of CRT + HIIT in the evening versus HIIT in the morning).i.CRT as well as sleep enhancement (i.e., HIIT in the early evening) as a six-week add-on therapy reduces connectivity strength in the salience network.

### Setting

Treatment-seeking participants with TUD according to the fifth version of the Diagnostic and Statistical Manual of Mental Disorders (DSM-5; [48]) will be randomised into four intervention arms. Assessments will take place before (baseline, T1) and after (second investigation day; T2) the six-week smoking cessation program, with a follow-up assessment (T3) three months later. A sport medical examination will be conducted at baseline at an outpatient cardiology clinic, while the other assessments will be conducted at the Central Institute of Mental Health, Mannheim, Germany.

### Study population and design

The study will be advertised by public advertisements and posters in the local community, newspaper outlets, websites and word of mouth. Interested candidates will undergo a short telephone screen to assess study eligibility and receive information about the study content and organization. A physical examination will then be conducted to ensure that participants are able to perform HIIT. Treatment-seeking smokers (men and women) aged between 18 and 65 years will be included in the study. The inclusion criteria will require prospective participants to meet at least four of the eleven TUD criteria according to the DSM-5, have a body mass index of between 18 and 35, demonstrate sufficient German proficiency to understand questions (both orally and in writing), communicate with investigators, and provide written consent. Additionally, participants must pass a physical examination to ensure that their participation in HIIT is safe. The exclusion criteria will apply to participants with severe somatic or neurological diseases and psychiatric comorbidities other than TUD according to the International Classification of Diseases (ICD-10) and DSM-5. A diagnosis of a sleep disorder (such as restless leg syndrome or insomnia) can also result in exclusion. Additionally, shift workers and night workers will be excluded. Participants will be excluded if they meet any of the following additional criteria: pregnancy and/or breastfeeding; high alcohol intake (screening scores with a score of 4 or higher for women or 5 (or higher) for men [49]); positive drug screening (e.g., amphetamine, benzodiazepine, cocaine, opioids); recent use of psychotropic medications (within the last 14 days, except stable adjusted SSRIs); medications affecting sleep, TUD, or physical activity (e.g., sleep medication, corticosteroids, stimulants); thyroid dysfunction or thyroid stimulation hormone levels outside the normal range; high blood pressure (resting heart rate > 100); or common MRI exclusion criteria (metal and claustrophobia).

A total of 128 participants will be randomized into four groups (4 × 32 smokers), receiving add-on interventions alongside a smoking cessation program (SCP) [50]. The randomization protocol will control for sex. Stratified (men/women) block randomization with permuted blocks of size 8 will be used. Groups 1 and 2 will receive CRT + HIIT either in the evening or morning, respectively. Group 3 and Group 4 will receive only HIIT in the evening or morning, respectively. Each subject will undergo three days of investigation. Assessments will occur before SCP (baseline, T1), after a six-week SCP (T2), and at a follow-up appointment three months later (T3). An in-house smartphone application will be used to remind participants about the exercises and to collect accompanying information, i.e., physical exertion (every training day), cigarette craving (3 times per week), and evaluation of the three interventions (three days per week). Instances of relapse and any sleep or physical problems can also be reported. These data will be stored on local servers at the institute, and no personal information will be collected. Between T2 and T3, biweekly telephone screenings will be conducted to assess abstinence or relapse, as well as the amount of cigarette consumption. See study schedule, Fig. 2.

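### The design section randomises 128, the number needed in the analysis, while the Abstract and sample-size section call for 140; stopping at 128 would remove the dropout allowance

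*Protocol article*

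**What the plan says.** Three places in the protocol article give the trial's size.

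- **Study population and design**, the paragraph that also sets out the sex strata and the blocks of 8: "A total of 128 participants will be randomized into four groups (4 × 32 smokers".
- **Sample size**: "With a sample size of 128 participants (32 participants per group), we achieve a power of 80" per cent, "assuming a minimum effect size of f = 0.25 in an ANOVA at a 5% alpha level". The calculation is made "on the basis of the number of days of abstinence at posttreatment (day 42"). For potential dropouts, "three participants per group will be added, resulting in a total population of 140 participants".
- **Abstract, Methods**: "The study will enrol 140 treatment-seeking smokers", followed by "The participants will be randomly assigned to four groups".

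Two other sections bear on how these can be read. Baseline Assessment (T1) says that, once screening and eligibility checks are done, all participants are allocated to one of the four arms and have their baseline assessment. The Discussion names a high dropout rate as the potential limitation of the study, without giving a figure.

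**The concern.** The Sample size section uses 128 as the number with outcome data needed for the stated power, and 140 as that number plus an allowance for loss. The design section takes the first figure and makes it the number randomised. Both cannot be the randomisation target.

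The number randomised fixes the length of the allocation lists, the point at which recruitment stops, and the figure against which completion of the trial will later be judged. If the design section is followed, the allowance of 12 participants never enters the trial. Any dropout then takes the analysed number below 128. With two totals in print, a reader also cannot tell whether a trial that stops at 128 is complete or 12 short.

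**Working it through.** **Inputs.** From Sample size: f = 0.25, α = 0.05, an ANOVA, 128 in total (32 per group), power 80%, plus three per group for dropout. From Study population and design: four equal groups, 128 randomised. The numerator degrees of freedom are not stated and have to be inferred.

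**Step 1: reproduce the plan's figure.** For a fixed-effects ANOVA with four cells, power is the probability that a noncentral F variable exceeds its 5% critical value, with noncentrality λ = f² × N and denominator degrees of freedom N − 4.

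- At N = 128: λ = 0.0625 × 128 = 8.0 and denominator df = 124.
- With 1 numerator df (a main effect or the interaction in the 2 × 2 layout), power is 0.801, and 128 is the smallest total that reaches 80%. This matches the plan.
- With 3 numerator df (an overall four-group test), power at 128 is 0.639 and 179 would be needed. This does not match.

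The 1-df reading is therefore used below. It confirms that 128 is the analysed number, with no slack built in.

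**Step 2: the allowance.** 4 × 3 = 12; 128 + 12 = 140 = 4 × 35; 12/140 = 8.6%. Inflating 128 for 8.6% loss, 128/(1 − 12/140), returns exactly 140.

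**Step 3: what each total delivers.** The 8.6% row is the plan's allowance expressed as a rate. All other rates are assumptions, because the article gives none. Power is evaluated at the expected number analysed, including fractions.

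| Loss | Analysed if 128 randomised | Power | Analysed if 140 randomised | Power |
|---|---|---|---|---|
| 0% | 128 | 0.801 | 140 | 0.836 |
| 5% | 121.6 | 0.781 | 133 | 0.816 |
| 8.6% | 117 | 0.765 | 128 | 0.801 |
| 10% | 115.2 | 0.758 | 126 | 0.795 |
| 20% | 102.4 | 0.707 | 112 | 0.746 |
| 30% | 89.6 | 0.648 | 98 | 0.688 |

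If exactly three per group are lost from 128, then 128 − 12 = 116 remain and power is 0.761.

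**Step 4: size of the effect.** At the plan's allowance, randomising 128 rather than 140 costs 0.801 − 0.765 = 0.036, or 0.801 − 0.761 = 0.040 if three per group are lost. Across the table the gap between the two totals stays between about 3 and 4 percentage points.

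**Step 5: can the sections be reconciled as written?** One reading is that 140 are enrolled and 128 are left to randomise after early losses. The text does not support it. The extra participants are added per group, and a person belongs to a group only after allocation. The Abstract makes the enrolled participants the ones who are randomised. Baseline Assessment (T1) describes no loss between eligibility and allocation. The power endpoint is at day 42, so the losses that matter include those during the six-week intervention, after randomisation.

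**The case against.** The strongest reply is that the intended total can be recovered. The Sample size section gives 128 and then 140 in a clear sequence, and the Abstract repeats 140. The design paragraph probably carries over the figure from before inflation, and nothing in it says that recruitment will stop at 128. On this view the inconsistency is editorial and the harm hypothetical.

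Several qualifications do stand:

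- With no dropout, 128 gives the stated power. The shortfall depends on loss.
- The 8.6% is an allowance converted to a rate, not a forecast made by the plan.
- The 1-df test is inferred from the fact that it reproduces the plan's figure.
- At 20% loss, 140 randomised would also fall short (0.746), so most of the deficit at that rate comes from the dropout itself. Only about 4 points come from the choice between 128 and 140.

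These limit the size of the point but do not remove it. The design paragraph is where the allocation procedure is defined, so it is the natural source for whoever prepares the lists, and it says plainly that 128 are randomised. Nor is this a detail that a condensed article leaves to a fuller document: the article states the figure, in two incompatible ways.

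**Conclusion.** The inconsistency is real. The design section gives the number needed in the analysis as the number randomised, while the Sample size section and the Abstract give 140. If 128 is followed and the planned allowance is lost, 116 to 117 participants remain and power is about 76% instead of 80%. At an assumed 20% loss it is about 71%, against about 75% with 140 randomised. These figures rest on f = 0.25, α = 0.05, a 1-df test and loss of the day-42 outcome. The effect on power is modest, but the correction should be made because the number randomised governs how the trial is run and reported.

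**What to change.** In Study population and design, state that 140 participants will be randomised (4 × 35) and describe 128 (4 × 32) as the number needed in the analysis. Prepare the sex-stratified lists to cover 140. Because blocks of 8 are filled within each sex stratum, final blocks may be incomplete whichever total is used, so 35 per arm should be described as a target. If the investigators do intend to randomise only 128, the Abstract and the Sample size section need correcting instead, with the lower expected power stated.

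The recommended change costs one corrected figure, one clarifying phrase and slightly longer allocation lists. It adds nobody beyond the 140 already planned.
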